However, the same comparison between intensities (progressive vs. constant) has not yet been performed in research on fibromyalgia, which leads to the question: does resistance training with progressive intensity, compared to constant intensity (on walking and resistance training), promote a greater reduction in the level of fibromyalgia impact? The answer to this question will characterize the scientific and social feedback of this research, which will provide subsidies to health professionals to adjust the intensity of resistance training and thus plan the most effective intervention (progressive or constant intensity; walking or resistance training) to reduce the impact of fibromyalgia in the lives of the patients.

The hypothesis is that progressive intensity resistance training in patients with fibromyalgia will produce a greater reduction in impact of fibromyalgia than constant intensity exercise (walking and resistance training). Thus, the aim of the study is to compare the effect of 24 sessions of resistance training (progressive intensity vs. constant-intensity) on impact of fibromyalgia after 24 sessions of resistance training, as well as the global perceived effect regarding treatment and impact of fibromyalgia during the intervention and after 3 months of non-exercise follow-up.

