### Outcomes

Primary outcome will be the comparison (among groups) of the effect of 24 sessions of resistance training (progressive intensity vs. constant intensity) on impact of fibromyalgia. Secondary outcomes will be to evaluate changes in sleep quality, anxiety, depression, cutaneous sensory threshold, wind-up mechanism, diffuse nociceptive inhibitory control, walking ability, musculoskeletal capacity after 24 sessions of resistance training, as well as global perceived effect and adherence regarding treatment and impact of fibromyalgia during the intervention and after 3 months of non-exercise follow-up (Fig. 2).

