### Statistical analysis

We will perform statistical analysis based on intention-to-treat analysis. We will use histograms and normality tests to verify the distribution of the data. Comparisons will be made through mixed linear models using interaction between factors time (before, during the intervention, after 24 exercise sessions, and 3 months after the end of treatment) and group (progressive intensity, constant intensity, and walking), besides, the baseline will be used as a covariate in the analyses [75]. Data will be presented as mean, standard-deviation, difference between means, confidence interval (95%) of these differences, and effect size (Cohen d). We will consider a significance level of 5% on the SPSS® software, version 17.0 (Chicago, IL, EUA) [76].

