## Discussion

### Potential impact and significance of the study

Exercise science has shown that progressive intensity resistance training generates better musculoskeletal adaptations than constant-intensity resistance training [77, 78]. These adaptations contribute positively to the physical function [13, 17], cognitive performance [4, 79], and patient quality of life [4]. However, these interventions [77, 78] and outcomes [4] have not yet been studied in patients with fibromyalgia [13, 17].

To our knowledge, this study will be the first clinical trial to compare resistance training intensity (progressive vs. constant) in patients with fibromyalgia. Therefore, the results will show the effectiveness (or not) of this proposal. In addition, as a randomized clinical trial, it will contribute to novel evidence syntheses in systematic reviews [17], as well as guidelines [4], generating more perspectives for evidence-based health [18, 19]. Besides, this study compares progressive intensity to two types of exercise (resistance and aerobic), thus filling two gaps simultaneously.

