### Contribution to professionals and patients

This study will provide health professionals with guidance in planning/applying resistance training [17] (with progressive intensity [77] or not) to reduce the impact of fibromyalgia [42], as we will find out if gradual exposure to resistance training [17] is more effective than constant exposure (to resistance training and/or walking) on patients’ rehabilitation. In addition, the results will also contribute to patients’ knowledge about non-pharmacological treatment of fibromyalgia [4] and whether the proposed types of exercise are significantly different on the primary outcome (impact of fibromyalgia [42]). In fact, if the results show insignificant differences [76] among the proposed exercises, patients with fibromyalgia will be able to choose the type and intensity of exercise according to their preferences [19, 20].

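### The protocol does not fix which comparison decides the primary hypothesis, and the group-by-time interaction it names does not answer that question

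*Protocol article*

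**What the plan says.** The Introduction states the hypothesis that progressive training "will produce a greater reduction in impact of fibromyalgia than constant intensity exercise (walking and resistance training"). The next sentence narrows this: "the aim of the study is to compare the effect of 24 sessions of resistance training (progressive intensity vs. constant-intensity) on impact of fibromyalgia".

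The Outcomes section reads "Primary outcome will be the comparison (among groups) of the effect of 24 sessions of resistance training (progressive intensity vs. constant intensity"), so it speaks of groups in general but names one pair. Footnote a of Table 1 does the same. Both place the primary comparison after 24 sessions, which is week 12. FIQ-R during the intervention and at the 3-month follow-up is classed as secondary.

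The Discussion, under the contribution to professionals and patients, says the trial will show whether gradual exposure "is more effective than constant exposure (to resistance training and/or walking"). Under potential impact it says "this study compares progressive intensity to two types of exercise (resistance and aerobic), thus filling two gaps simultaneously".

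The Statistical analysis section says "Comparisons will be made through mixed linear models using interaction between factors time" and group, with four time points, three groups and baseline as a covariate. It plans to report the "difference between means, confidence interval (95%) of these differences, and effect size (Cohen d") and sets one level for everything: "We will consider a significance level of 5% on the SPSS® software".

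**The concern.** Three different rules for success can be read from the same document: one contrast, both contrasts, or either. The analysis section does not choose among them, and the test it names covers all arms and visits at once.

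Two things are at stake. First, a significant interaction could be taken as support for progression when progressive and constant training did not differ at week 12. Second, if only one of the two contrasts turns out significant, nothing settles whether the hypothesis was confirmed. This matters for interpretation because progressive versus walking also changes the type of exercise. Only progressive versus constant resistance training isolates progression of intensity.

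**Working it through.** **1. The statements side by side**

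| Place | Comparator(s) for progressive training | Rule implied |
|---|---|---|
| Introduction, hypothesis | constant resistance training and walking | both, on the natural reading |
| Introduction, aim | constant resistance training | single contrast |
| Outcomes; Table 1 footnote a | among groups, but only constant resistance training is named | single contrast, with some ambiguity |
| Discussion, contribution to professionals and patients | resistance training and/or walking | either or both |
| Statistical analysis | none named | none |

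**2. What the interaction tests**

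Its null hypothesis is that the differences between arms are the same at every time point. With three groups and four time points it has (3 − 1) × (4 − 1) = 6 degrees of freedom. If baseline enters only as a covariate, three visits remain and it has (3 − 1) × (3 − 1) = 4.

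This null is false in each of the following cases, although progressive and constant training do not differ at week 12:
- the two resistance arms are identical throughout, and walking differs at week 12;
- all arms agree up to week 12, and one differs at the no-exercise follow-up.

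Conversely, in the 4-df form a benefit of equal size at weeks 6, 12 and 24 produces no interaction, because it lies in the group effect. In neither direction does the result answer the primary question.

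**3. Error rate under each possible rule**

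Inputs: 5% level (Statistical analysis) and 1:1:1 allocation (Randomization, allocation, and blinding). There are 21 per arm (Sample size), or about 18 after the planned 15% loss (21 × 0.85 = 17.85). Assumptions: two-sided tests, since the protocol does not state sidedness, and equal variances.

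A single contrast gives the plan's 5%: 4.97% and 4.98% by simulation with 18 and 21 per arm (1 million runs).

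The two contrasts share the progressive arm. Their covariance is σ²/n and each variance is 2σ²/n, so their correlation is (σ²/n) / (2σ²/n) = 0.5.

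- *Either suffices, no true differences:* 1 − P(|Z₁| ≤ 1.96 and |Z₂| ≤ 1.96) at correlation 0.5 = 9.1%. With t tests at 18 or 21 per arm it is 9.0%. The Bonferroni upper bound is 10%.
- *Both required, no true differences:* 5% + 5% − 9.1% = 0.9%.
- *Both required, one difference truly large:* the error is that of the other test alone, 5.0%. This is the maximum.
- *Progressive versus constant only:* 5%.

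Counting only false claims in favour of progressive training, the either-rule gives 4.5%, against 2.5% for a single two-sided test.

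**4. A fixed sequence**

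If progressive and constant training truly do not differ, any false claim requires rejecting that first test, which happens at most 5% of the time. If they do differ, only the walking test can be falsely positive, again at most 5%. No adjustment of either level is needed.

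**The case against.** The strongest reply is that the protocol already says enough. Progressive versus constant resistance training is the only pair named in the aim, the primary outcome and Table 1. The time point is fixed and the other FIQ-R visits are secondary. The analysis section is not confined to an interaction: it also plans a baseline covariate and mean differences with confidence intervals. Testing order and multiplicity adjustment are commonly left to a statistical analysis plan, which is not shown here.

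Most of this stands. The absence of a multiplicity procedure from a condensed article would not be a finding on its own, and setting progressive training against walking is a legitimate comparative question. What remains is a conflict within the text shown. The hypothesis and the Discussion bring walking into the claim in two different ways, and no planned mean difference is named as the one that decides.

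A reader might infer that the error rate for the primary claim exceeds 5%. The documents do not support that: with no rule fixed, no single error rate follows, and only the either-rule exceeds 5%. Nor would it be right to quote larger rates by adding constant versus walking, which is outside the hypothesis, or the other visits, which are already secondary. A general loss of power from using the interaction is not shown either, since any such figure depends on an effect size and a between-visit correlation that the protocol does not give.

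**Conclusion.** The point holds as an inconsistency about what decides the trial, together with a named test that does not match the primary outcome. Its size is conditional: familywise error of about 9% if either unadjusted week-12 contrast may carry the claim, and at most 5% if both are required or if progressive versus constant stands alone. These figures assume two-sided tests, equal arms and equal variances. The argument about the interaction needs no numerical assumption. This is a cheap improvement that should be made. It does not show that the plan, as written, has an inflated error rate.

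**What to change.** Reconcile the Introduction, Outcomes, Statistical analysis and Discussion with text such as: *The primary test is the baseline-adjusted difference in FIQ-R at week 12 between progressive and constant resistance training, from the mixed model, at two-sided 5%. Progressive training versus walking at week 12 will be tested at two-sided 5% only if the primary test is significant.*

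Treat the group-by-time interaction and the constant-versus-walking pair as secondary, reported with estimates and 95% confidence intervals, as FIQ-R at other visits already is. Base conclusions about progression on the first contrast alone.

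Requiring both contrasts would also control the error and fits the literal hypothesis. The sequence is preferable because it follows the stated primary outcome and keeps the full 5% for the question the trial calls new.

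The cost is a few sentences, with no added participants, visits or data. The downside is that no confirmatory claim against walking can be made if the first contrast is not significant.

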## Discussion

### Potential impact and significance of the study

Exercise science has shown that progressive intensity resistance training generates better musculoskeletal adaptations than constant-intensity resistance training [77, 78]. These adaptations contribute positively to the physical function [13, 17], cognitive performance [4, 79], and patient quality of life [4]. However, these interventions [77, 78] and outcomes [4] have not yet been studied in patients with fibromyalgia [13, 17].

To our knowledge, this study will be the first clinical trial to compare resistance training intensity (progressive vs. constant) in patients with fibromyalgia. Therefore, the results will show the effectiveness (or not) of this proposal. In addition, as a randomized clinical trial, it will contribute to novel evidence syntheses in systematic reviews [17], as well as guidelines [4], generating more perspectives for evidence-based health [18, 19]. Besides, this study compares progressive intensity to two types of exercise (resistance and aerobic), thus filling two gaps simultaneously.

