### Strengths and weaknesses of the study

The strength of this study will be the comparison of the progressive intensity of resistance training with the constant intensity of two types of exercise (resistance training and walking). In contrast, the weakness of this research will be the impossibility of blinding the therapist and the patient during the treatment, considering that the intervention type (physical exercise) will be observed by both.

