### Prospects for future research

Although this study focuses on the investigation of exercise intensity on the impact of fibromyalgia [42], there is still a need for future studies to propose ways to compare different types of exercise (e.g., resistance training vs. walking), as we know that musculoskeletal adaptations result from the physical effort performed (not the type of exercise proposed) [71]. This means that further studies investigating different exercise types should develop strategies or methods to monitor the total physical effort performed in each exercise program [72].

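### A conclusion on progressive versus constant intensity should rest on Group 1 minus Group 2 alone; the wording lets a difference from walking support it too

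*Protocol article*

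**What the plan says.** The Introduction asks whether progressive resistance training, "compared to constant intensity (on walking and resistance training), promote a greater reduction in the level of fibromyalgia impact". It then hypothesises that progressive training "will produce a greater reduction in impact of fibromyalgia than constant intensity exercise (walking and resistance training"). Its closing aim is narrower: progressive against constant resistance training. The Outcomes section words the primary outcome in the same narrow way, though as a comparison among groups.

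The Discussion returns to the wider framing:

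- Potential impact and significance: "this study compares progressive intensity to two types of exercise (resistance and aerobic), thus filling two gaps simultaneously".
- Contribution to professionals and patients: the trial will show whether gradual exposure "is more effective than constant exposure (to resistance training and/or walking"). The results are also to show whether the exercise types differ on the primary outcome.
- Strengths and weaknesses: the strength is the "comparison of the progressive intensity of resistance training with the constant intensity of two types of exercise (resistance training and walking"). The only weakness listed is that therapist and patient cannot be blinded.
- Prospects for future research: "there is still a need for future studies to propose ways to compare different types of exercise (e.g., resistance training vs. walking"), and such studies "should develop strategies or methods to monitor the total physical effort performed in each exercise program".

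The Statistical analysis section plans a mixed linear model with a time-by-group interaction over three groups. It reports differences between means with 95% confidence intervals.

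**The concern.** Calling walking a constant-intensity comparator puts two questions under one label. Group 1 against Group 2 asks whether progression helps within resistance training. Group 1 against Group 3 asks whether one whole program beats another. If resistance training of either kind outperformed walking and progression added nothing, the and/or wording would still allow the report that gradual exposure beats constant exposure. The stated purpose is to help professionals choose how to set resistance intensity, so this would credit progression with an effect that belongs to the type of exercise.

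There is also a tension over exercise type. The Introduction and the Contribution subsection promise information on walking versus resistance training, while the Prospects subsection leaves ways of comparing these types to later studies.

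**Working it through.** **What differs between the arms** (Group 1 to Group 3 subsections and Table 2)

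| Arm | Type | Intensity scale | Progression |
|---|---|---|---|
| Group 1 | resistance | % of 1-RM | 50, 70, 90% |
| Group 2 | resistance | % of 1-RM | none, 50% |
| Group 3 | treadmill walking | % of HRmax | none, 60-70% |

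For the group means:

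G1 − G3 = (G1 − G2) + (G2 − G3)

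The first term is progression. The second is exercise type, including the change of intensity scale and any difference in total effort. G1 − G3 equals the progression effect only if the second term is zero.

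**The plan's own figure.** The Sample size section gives 63 in total (f = 0.41, 95% power, 5% significance, three groups, four time points). The between-groups repeated-measures formula is λ = f²·N·m / (1 + (m − 1)ρ). With an assumed ρ = 0.5, which the article does not state, λ = 0.1681 × 63 × 4 / 2.5 = 16.94 and power is 0.958. The stated 63 reproduces and is not in dispute.

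**Illustration.** From the Sample size section: SD 16.3, 21 per arm, 5% significance (taken as two-sided). Assumed: no progression effect (G1 = G2), and both resistance arms better than walking by D points. The article gives no value for D.

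- Standard error of a pairwise difference: 16.3 × √(2/21) = 5.03.
- Noncentrality: D / 5.03. Critical t on 40 degrees of freedom: 2.021.

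| D | Noncentrality | G1 − G3 significant | Of all trials: G1 − G3 significant, G1 − G2 not |
|---|---|---|---|
| 8 | 1.59 | about 34-35% | 32% |
| 10 | 1.99 | 49% | 47% |
| 13.4 | 2.66 | 74% | about 70% |

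The last column is simulated. G1 − G2 is significant in the favourable direction in 2.5% of trials whatever D is, because its true value is zero. If wins over both comparators are required, the chance cannot exceed that 2.5%.

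With 15% loss (21 × 0.85 = 17.85, so 18 per arm), the G1 − G3 rates are 30%, 43% and 67%. Baseline adjustment at an assumed correlation of 0.5 reduces the SD by √(1 − 0.25); with 21 per arm the rates are then 43%, 61% and 85%.

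**The case against.** The case on the other side is substantial, and much of it stands.

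- A reader might infer that the protocol formally counts a win over walking as proof of progression. It does not. No section sets such a rule, and the sentence about two gaps merely describes two comparisons. The Objective, the aim and the primary outcome all name progressive against constant resistance training, and in the arm names and the model constant intensity means Group 2 alone.
- The hypothesis joins walking and resistance training with "and", which reads naturally as needing both wins. Under that reading the illustrated risk disappears.
- A reader might infer that Group 2 minus Group 3 will go unused. Nothing excludes it: the model contains all three groups, and an article need not list every pairwise contrast.
- A reader might take the Prospects subsection as saying that the types cannot be compared. It says that ways to do so are still needed. That sits uneasily with the promises elsewhere but does not flatly contradict them.
- The percentages are ordinary power to detect a real difference between Groups 1 and 3, not an error rate of the planned model. Group 1 minus Group 2 would be reported beside it with its interval.

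What this does not remove is the and/or in the Contribution subsection, which allows walking alone to carry the claim, and the constant-intensity label on walking in the Introduction and the Strengths subsection.

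**Conclusion.** The point holds as one about interpretation. The design contains the right contrast for progression and the aim names it; the wording around it lets a second, confounded contrast stand in. Under the assumptions shown, Group 1 minus Group 3 would be significant in about 35% to 74% of trials in which progression does nothing, against 2.5% in the favourable direction for Group 1 minus Group 2. Those figures depend on an assumed type effect of 8 to 13.4 points, SD 16.3, 21 per arm and a single time point, and they matter only if a win over either comparator is accepted. The planned model and the sample size are not at fault here.

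One limit on the preferred contrast: the Group 1 and Group 2 subsections also list the exercises in a different order and give different rest between sets from the second month. The longer rest is explained in the text; the order is not and should be reconciled.

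**What to change.** In the Introduction and in the Contribution and Strengths subsections of the Discussion:

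1. State that any conclusion on progressive versus constant intensity rests on Group 1 minus Group 2 alone.
2. Assign the exercise-type question to Group 2 minus Group 3, both constant, with the caveat from the Prospects subsection that total effort is not equated.
3. Report Group 1 minus Group 3 as a comparison of whole programs that is not evidence for progression.
4. Remove the and/or reference to walking from the progression claim.

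All three contrasts come from the planned model, so no data, participants or analyses are added. The cost is a narrower claim from the walking comparison.

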### Contribution to professionals and patients

This study will provide health professionals with guidance in planning/applying resistance training [17] (with progressive intensity [77] or not) to reduce the impact of fibromyalgia [42], as we will find out if gradual exposure to resistance training [17] is more effective than constant exposure (to resistance training and/or walking) on patients’ rehabilitation. In addition, the results will also contribute to patients’ knowledge about non-pharmacological treatment of fibromyalgia [4] and whether the proposed types of exercise are significantly different on the primary outcome (impact of fibromyalgia [42]). In fact, if the results show insignificant differences [76] among the proposed exercises, patients with fibromyalgia will be able to choose the type and intensity of exercise according to their preferences [19, 20].

